### Outcomes and others measures

#### Primary outcome measures

The **primary outcome measures relating to objective 1 **include the description of the implementation of preventive services according to the PAPPS criteria [6].

Screening for smoking status: if there is information on the consumption of tobacco over the last two years in members of the population who previously were non-smokers.

Screening for excessive alcohol consumption: if there is information on the consumption of alcohol over the last two years in members of the population who previously were not high consumers of alcohol.

Screening for obesity: if there have been measurements of height and weight or body mass index (BMI) over the last 4 years in members of the population who previously were non-obese.

Screening for hypertension: if there is information on systolic blood pressure (BPS) and diastolic blood pressure (BPD) during the last 4 years in members of the population aged between 16 and 40 years who previously did not have the diagnosis of hypertension; or over the past 2 years in members of the population older than 40 years who previously did not have the diagnosis of hypertension.

Screening for hypercholesterolemia: if there is information on total blood cholesterol corresponding to the following criteria of age and gender: 1 measurement in males between 16–35 years old; 1 measurement in females between 16–45 years old; 1 measurement every 5 years in males between 35–75 years old; 1 measurement every 5 years in females between 45–75 years old; 1 measurement if there has not been a previous measurement in those older than 75; all of these performed in population that previously did not have the diagnosis of hypercholesterolemia.

Anti-tetanus vaccination (ATV): if there is a registry of anti-tetanus vaccination over the previous 10 years.

Anti-influenza vaccination (AIV): if there is a registry of annual anti-influenza vaccination in those older than 59 years of age.

The **primary outcome measures relating to objective 2 **describes the clinical follow-up of the five health problems identified up to December 31^st ^2007 and evaluated up to December 31^st ^2008:

Evolution of tobacco consumption: quit smoking or remaining an ex-smoker.

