#### Secondary outcome measures

Number of different preventive services (among the 7 of the study) registered for each individual during the 2006 and 2007 year periods.

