### Statistical analyses

For the first two objectives all the analyses will be performed on a global level and each region separately. Cluster level analysis (computerized PHCT and health-care professional) will be performed using standard parametric or non-parametric analytical methods, with cluster means or proportions as observations [37,42]. For the adjusted analysis we will perform regression analysis of individual level data using methods for clustered data, multilevel, hierarchical or random effects models [37,43]. This methodology facilitates simultaneous analyses of the effects of individual and cluster variables in order to evaluate whether the relationship between variables at the individual level varies in accordance with the characteristics of the cluster and whether the individual and cluster variability can be attributed to factors of the cluster and/or to the factors related to the individual. Analysis will be performed at 3 levels: PHCT, health-care professional and individual subjects.

Multilevel linear (for continuous outcome variables) or logistic (for dichotomous outcome variables) regression analyses will be performed for the first two objectives. The analyses will be adjusted for explanatory factors at individual, health-care professional and PHCT level and for other variables that are clinically relevant. We will also adjust for possible confounders checking whether they will affect the outcomes. A nested or hierarchical structure will be considered: the attended individuals are nested within the health-care professional and the health-care professional within PHCT. The PHCT and the health-care professional will be considered random effects.

Multilevel Poisson regression models will be used to evaluate the number of preventive activities recorded for each individual.

For the third objective, the ICCs, their standard errors and the components of variance [36,37,42,43] for the different outcome measures will be calculated using methods that enable adjustment for covariables, together with random effect methods (health-care professionals and PHCT). Initially, we will estimate the coefficients of variance and ICCs using the outcome as the dependent variable and the health-care professional/PHCT as random effects. Subsequently, we will perform an adjusted analysis for the characteristics of the individual, the health-care professional and the PHCT.

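### The secondary count of preventive services has no eligibility denominator, so its Poisson model can show associations with age, and possibly with known disease, when care is identical

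*Protocol article*

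**What the plan says.** Under Secondary outcome measures, the protocol article defines the outcome as "Number of different preventive services (among the 7 of the study) registered for each individual during the 2006 and 2007 year periods". Under Statistical analyses it fixes the model: "Multilevel Poisson regression models will be used to evaluate the number of preventive activities recorded for each individual". The Design part of the Abstract also names Poisson multilevel models for this count. None of these places gives a denominator, an offset or an upper bound.

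Under Primary outcome measures, the seven services have unequal target groups:

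- Influenza vaccination counts "if there is a registry of annual anti-influenza vaccination in those older than 59 years of age".
- Smoking screening is for "members of the population who previously were non-smokers".
- Alcohol screening is for "members of the population who previously were not high consumers of alcohol".
- Obesity screening is for "members of the population who previously were non-obese".
- Hypertension and hypercholesterolemia screening are likewise limited to people without an earlier diagnosis of that condition.
- Only tetanus vaccination is defined for everyone.

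Other measures lists gender, age, Adjusted Clinical Groups (ACG) comorbidity and consultation frequency as patient-level factors. The number of services a patient is eligible for is not among them.

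**The concern.** A service for which a patient does not qualify adds nothing to the count, just like a service that was due and not given. The count therefore mixes two things: how many services were due, and how many of those were recorded. Objective 1 asks which factors relate to implementation, and age and comorbidity are among the factors to be examined. If they also determine how many services are attainable, their rate ratios will partly describe eligibility and be read as differences in care. With more than 850,000 subjects planned, even a modest artefact is likely to be significant at the plan's 1% level.

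For objective 3, variance components and ICCs are first estimated without covariates. For this outcome they would also carry differences in eligibility case mix between professionals and teams.

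A second, lesser matter is the distribution. A count that cannot exceed seven is not Poisson, and at high delivery rates its variance is well below its mean.

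**Working it through.** The article gives no figure for this model, so there is none to reproduce.

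**1. Attainable number per patient** (Primary outcome measures, assuming its restrictions govern the count)

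- Over 59, no known condition: 7.
- 59 or younger, no known condition: 6.
- Each known condition removes one. With all five, 2 remain above 59 and 1 at 59 or younger.

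**2. Age artefact with identical care**

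With a common delivery rate p, the expected count is p × (number eligible). For patients with no known condition, 59 or younger against older, the ratio is 6p/7p = 0.86 for any p.

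The Background, on preventive services in primary care, reports 92.8% for the hypertension, smoking and alcohol group and more than 70% for the other four services. Taking 92.8% and 70% as the rate of each service (an assumption):

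- Over 59: 3 × 0.928 + 4 × 0.70 = 5.58.
- 59 or younger: 3 × 0.928 + 3 × 0.70 = 4.88.
- Ratio: 4.884/5.584 = 0.875.

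**3. Single-factor artefacts in a mixed population**

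Assumed, not from the documents: 30% aged over 59; smoking 27%, high alcohol use 5%, and hypertension, hypercholesterolemia and obesity 20% each; all independent of one another and of age; common p.

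- Mean conditions per patient: 0.27 + 0.05 + 3 × 0.20 = 0.92.
- Mean eligible services: 7 − 0.70 − 0.92 = 5.38.
- Over 59 against younger: (7 − 0.92)/(6 − 0.92) = 6.08/5.08 = 1.20.
- Hypertension known against not: (5.58 − 1)/5.58 = 4.58/5.58 = 0.82, where 5.58 = 5.38 + 0.20.
- Smoker against not: (5.65 − 1)/5.65 = 4.65/5.65 = 0.82, where 5.65 = 5.38 + 0.27.

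A simulation of 200,000 patients with these prevalences and p = 0.75 gave the same rate ratios (1.20, 0.82, 0.82) with all three factors in the Poisson model. Adding log(number eligible) as an offset gave 1.00 for each, but Pearson dispersion was 0.25. A binomial model of recorded out of eligible gave odds ratios of 1.00, 0.99 and 1.00 with dispersion 1.00. Clustering was left out because it does not bear on this point.

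**4. Variance**

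Six eligible services at an assumed 70%: mean 6 × 0.7 = 4.2, the variance Poisson assumes. With within-patient correlation r between services, the actual variance is 6 × 0.7 × 0.3 × (1 + 5r) = 1.26(1 + 5r). The inflation of model-based standard errors is √[4.2 / (1.26(1 + 5r))]:

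| r | variance | factor |
|---|---|---|
| 0 | 1.26 | 1.83 |
| 0.2 | 2.52 | 1.29 |
| 0.3 | 3.15 | 1.15 |
| 0.47 | 4.22 | about 1.0 |

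**5. Does a simple proportion cure it when rates differ by service?**

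Use the 92.8% and 70% rates of step 2. A healthy 30-year-old has a proportion of 4.884/6 = 0.814. A 65-year-old smoker with hypertension, hypercholesterolemia and obesity is left with alcohol, tetanus and influenza: (0.928 + 2 × 0.70)/3 = 0.776. The odds ratio is (0.776/0.224)/(0.814/0.186) = about 0.79. The ratio of raw counts is 2.328/4.884 = 0.48, while the ratio of proportions is 0.776/0.814 = 0.95. The denominator removes most of the artefact but not all. A term for service type removes the rest, because with identical care the log odds then depend on the service alone.

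**The case against.** The other side has several sound points.

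- **It is a secondary outcome.** The seven single-service outcomes carry their own target groups and go into logistic models. This stands and lowers the severity.
- **The article is condensed, and Poisson does not exclude an offset.** This is true of the offset. But the article itself defines a raw count among seven and names the model family, and that specification gives the artefact if followed as written.
- **The plan adjusts for individual factors.** It does, but adjustment for age and ACG comorbidity puts the artefact into the coefficients that objective 1 interprets. For team comparisons the objection has more force. With the assumed mean of 5.38 eligible services, a 10-point difference between teams in one condition shifts the expected count by 0.1/5.38 = 1.9% before adjustment.
- **The known-disease part rests on a reading.** The secondary outcome does not say that the disease-free restrictions govern it, and its 2006 and 2007 window differs from the look-backs of up to ten years in the primary definitions. If a blood pressure recorded in a known hypertensive patient counts, that part falls away. The influenza age limit remains.

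A reader might infer stronger claims that the documents do not support:

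- **That sicker patients will look half as well served.** A ratio near 0.5 does arise (2.1/4.2 at a flat 70%), but only between a healthy 30-year-old and a 65-year-old with four conditions. Single-factor effects are much smaller.
- **That teams recording more diagnoses will be ranked as delivering less prevention.** No team-level bias of that size is shown.
- **That standard errors are wrong by a fixed 1.8 times.** That needs independent services within a patient. Several services recorded at one visit would plausibly be correlated, and the error is in the conservative direction.

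**Conclusion.** The concern holds as a should-fix on the secondary outcome. As written, the raw count and its Poisson model produce associations without any difference in care. The age effect (0.86 for 59 or younger against older at a common delivery rate, no known conditions) needs only the influenza age limit. The effect of one known condition (about 0.82) needs the assumed prevalences and the reading that the primary definitions govern the count. Unadjusted variance components and ICCs for this outcome also carry eligibility case mix. The size of any team-level bias is not established and is probably small after adjustment.

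The missing upper bound matters less. It makes standard errors conservative by an amount that depends on within-patient correlation and vanishes near r = 0.47 in the example. The bias comes from the missing denominator, not from the variance. The single-service primary analyses and objective 2 are untouched.

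**What to change.** Define the outcome as services recorded out of services for which the patient is eligible. State explicitly that the eligibility rules and look-back windows of the primary outcome definitions apply to it.

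Preferred analysis: a multilevel logistic model on patient-by-service records, eligible services only, with service type as a fixed effect and random effects for patient, professional and PHCT.

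Simpler alternative: a multilevel binomial model of recorded out of eligible, with professional and PHCT random effects and a dispersion check. The text should then note that a small residual artefact remains where delivery rates differ by service.

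Cost: one denominator derived from data already being extracted. The preferred model is heavier to fit (for 850,000 subjects, at most 7 × 850,000 = 5.95 million records). The result is reported as a proportion or odds ratio instead of a count; the raw count can still be shown descriptively by age group.

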### Sample size and randomisation

To achieve the equivalent power of a patient-randomised design, in a cluster randomised design the effective sample size will need to be the standard sample size of a single random sampling multiplied by the design effect [31,37,38]. The design effect is a function of the average cluster (computerized PHCT) size and the (intraclass correlation coefficient (ICC) of the outcome:

design effect = 1 + (n-1)*ICC

where *n *is the average number of individuals sampled per cluster [38].

sWith the cluster design we set an ICC of 0.05 on the assumption that the ICCs estimated for outcome variables from PC are less than 0.05 [28,36,39] and that the average number of individuals sampled per centre is at least of 2,500. Therefore 20 computerized PHCTs are necessary from each region to guarantee a statistical power of 80%, assuming a 50% event rate with an alpha two-tailed significance level of 0.05. Finally, to allow any of the randomised computerized PHCTs declining our offer to participate, we increased the number of computerized PHCTs selected from each region to 22. As such, the total number of subjects included will be more than 300,000 in Aragón, 200,000 in Navarra and 350,000 in Catalunya i.e. more than 850,000 subjects in total. This volume of subjects ensures a good estimate of the different outcome measures in the sub-groups of each cluster.

The selection of computerized PHCT to participate in the study is by a simple random sample within each region. Sample size calculation and computerized PHCT selection is performed with Epidat 3.1.

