We will study interactions and collinearity. The collinearity of the maximal models will be evaluated using the criteria proposed by Belsley [44]. We will set the significance level at 1% (two-tailed).

Analysis will be carried out using the SPSS statistical package for Windows, version 15 (SPSS Inc., Chicago, IL) and the SAS package 9.1.3 for Windows (SAS Institute Inc., Cary, NC, USA).

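### The 80% regional power is calculated at a two-sided 5% level but the analysis level is 1%; at 1% the same regional comparison has about 59% power

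*Protocol article*

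**What the plan says.** Two sections of the protocol article fix a significance level, and the values differ.

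- **Sample size and randomisation.** "Therefore 20 computerized PHCTs are necessary from each region to guarantee a statistical power of 80" per cent, "assuming a 50% event rate with an alpha two-tailed significance level of 0.05". The other inputs are an assumed intraclass correlation ("we set an ICC of 0.05 on the assumption that the ICCs estimated for outcome variables from PC are less than 0.05"), a cluster size ("the average number of individuals sampled per centre is at least of 2,500") and the usual inflation formula, "design effect = 1 + (n-1)*ICC". To cover refusals, "we increased the number of computerized PHCTs selected from each region to 22". No difference to be detected and no comparison is named.
- **Statistical analyses.** The section closes, after remarks on interactions and collinearity, with "We will set the significance level at 1% (two-tailed". It gives no other significance level.

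The analysis section also plans every analysis for the first two objectives both globally and separately by region, and it uses team means or proportions as observations in the cluster-level analysis. The per-region power claim therefore bears on analyses that will be carried out.

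**The concern.** Both levels are two-sided, both are current text, and neither refers to the other. A test sized at 5% and carried out at 1% does not have the power it was sized for. This is not detail that a fuller protocol or analysis plan might supply, because the article itself gives two values for one parameter.

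What is at stake is how a null result in a single region is read. If a team characteristic is not significant at 1%, a reader who relies on the sample-size section will credit that test with 80% power when it has less. The two values also leave unclear which threshold governs a p-value between 0.01 and 0.05.

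**Working it through.** **Inputs from the article.** Two-sided alpha 0.05 for sizing and 0.01 for analysis; power 0.80; 20 teams per region (22 selected); intraclass correlation 0.05; 2,500 subjects per team; event rate 50%. Normal quantiles: z(0.975) = 1.960, z(0.995) = 2.576, z(0.80) = 0.842.

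**Step 1. The plan's own figure.** Design effect = 1 + (2,500 − 1) × 0.05 = 125.95. Effective sample per region = 20 × 2,500 / 125.95 = 397. The count of 20 teams cannot be derived further without a difference to detect, and none is given. Two readings fit, and both are my assumptions:

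- 50% versus 60% between two groups of teams needs 388 subjects per group under simple sampling, and 388 × 125.95 / 2,500 = 19.5, so 20 teams per group.
- A 95% confidence interval for a 50% rate has half-width 1.96 × 0.5 / √397 = 0.049, or 4.9 percentage points.

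The next steps need neither reading. They take the stated 80% at 5% as given.

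**Step 2. Power at 1%.** A two-sided test with 80% power at 5% has a standardised effect of 1.960 + 0.842 = 2.802, whatever the raw difference. At 1%:

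Power = Φ(2.802 − 2.576) = Φ(0.226) = 0.589, about 59%.

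**Step 3. All 22 teams take part.** The standardised effect grows by √(22/20) = √1.1:

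Power = Φ(2.802 × √1.1 − 2.576) = Φ(0.363) = 0.64.

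**Step 4. Detectable difference at 1%.** To keep 80% power with 20 teams, the difference must grow by (2.576 + 0.842) / 2.802 = 3.418 / 2.802 = 1.22, that is by 22%. At a fixed difference, the number of teams would have to grow by 1.22² = 1.49, from 20 to about 30 per region.

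**Step 5. Where the 59% does not apply.**

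- *Pooled analysis.* Assume a common effect and the same intraclass correlation in three regions of 20 teams. Power at 1% is then Φ(2.802 × √3 − 2.576) = Φ(2.28), about 99%.
- *Lower intraclass correlation.* At 0.03 the design effect is 1 + 2,499 × 0.03 = 75.97 and the effective sample is 50,000 / 75.97 = 658. Power at 1% is Φ(2.802 × √(658/397) − 2.576) = Φ(1.03), about 85%. The same change would raise the power at 5% too, so the gap between the two levels remains.

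A t reference distribution would give somewhat less than 59%. Its degrees of freedom depend on a comparison that the article does not name, so I have not relied on it.

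**The case against.** The strongest reply has four parts.

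**Direction.** A stricter analysis level is conservative. It invalidates no test and inflates no false-positive rate, and with seven plus five primary outcomes and many candidate factors it is a defensible choice. This stands, and it is why the point is about the power statement and not about the 1% level.

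**Reach.** A reader might infer that the whole study has 59% power, or that about two in five effects of the planned size will be missed. The documents support neither. The 80% is a per-region figure, the pooled analysis is far better placed (Step 5), and no planned effect size is stated. A reader might also carry the 59% over to professional-level factors. The design effect covers clustering by team only, professionals are nested within teams with their own random effect, and no 80% was ever claimed for factors that vary within a team. The descriptive results and the intraclass-correlation estimates do not depend on a test level. All of this stands and limits the point.

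**Precision, not power.** Because 20 teams also fit a 4.9-point half-width, the calculation may have been about precision. The article nevertheless states a power and an alpha, and that statement is what a reader will use.

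**Scope of the 1% sentence.** It follows the sentences on interactions and collinearity and might have been meant for those. Its wording carries no such limit, and collinearity criteria are diagnostics, not significance tests. If the narrower meaning was intended, the level for the main analyses is unstated and the text still needs correcting.

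**Conclusion.** The point holds within limits. The article attaches 80% power to a two-sided 5% level and then sets 1% for the analysis without reconciling them. For the regional comparison that the 80% describes, power at 1% is about 59% with 20 teams and about 64% with 22; equivalently, the difference detectable with 80% power is about 22% larger.

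This rests on the stated 80% being correct at 5%, on the normal approximation, and on the article's intraclass correlation of 0.05. It does not depend on the unstated effect size. Since the article expects true intraclass correlations below 0.05, the 59% is the consequence of the plan's own assumptions and not a forecast of the power that will be achieved.

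**What to change.** Keep the 1% level and revise the sample-size section so that it describes the tests actually planned. Either say that 20 teams per region give about 59% power at a two-sided 1% level for the comparison that had 80% at 5%, or give the detectable difference at 1% with 80% power, which is 22% larger. Naming the comparison and the difference in the same sentence would let a reader reproduce the count.

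If 1% was meant only for interaction tests, say so in the analysis section and state the level for the main analyses.

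Moving the analysis to 5% would also make the sections agree, but it loosens error control across twelve primary outcomes and many factors merely to match a planning figure, so I do not recommend it on this ground alone.

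The cost is a sentence or two and a less favourable stated power. No extra teams are asked for. The roughly 30 per region that would restore 80% at 1% could not be found in Aragón in any case: the Setting section gives 19% of 121 teams as computerised, and 0.19 × 121 is about 23.
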